## Abstract

**Background:**

Post-stroke cognitive and emotional complications are frequent in the chronic stages of stroke and have important implications for the functionality and quality of life of those affected and their caregivers. Strategies such as mindfulness meditation, physical exercise (PE), or computerized cognitive training (CCT) may benefit stroke patients by impacting neuroplasticity and brain health.

**Materials and methods:**

One hundred and forty-one chronic stroke patients are randomly allocated to receive mindfulness-based stress reduction + CCT (*n* = 47), multicomponent PE program + CCT (*n* = 47), or CCT alone (*n* = 47). Interventions consist of 12-week home-based programs five days per week. Before and after the interventions, we collect data from cognitive, psychological, and physical tests, blood and stool samples, and structural and functional brain scans.

**Results:**

The effects of the interventions on cognitive and emotional outcomes will be described in intention-to-treat and per-protocol analyses. We will also explore potential mediators and moderators, such as genetic, molecular, brain, demographic, and clinical factors in our per-protocol sample.

**Discussion:**

The MindFit Project is a randomized clinical trial that aims to assess the impact of mindfulness and PE combined with CCT on chronic stroke patients’ cognitive and emotional wellbeing. Furthermore, our design takes a multimodal biopsychosocial approach that will generate new knowledge at multiple levels of evidence, from molecular bases to behavioral changes.

**Clinical trial registration:**

www.ClinicalTrials.gov, identifier NCT04759950.

## Introduction

Stroke is a leading cause of disability worldwide (Feigin et al., 2017). Advances in acute treatment have increased the number of people surviving a stroke which, in turn, has led to a growth in the number of patients with long-term consequences. It is estimated that up to 50% of stroke survivors experience some degree of disability at chronic stages of the disease, which jeopardizes functionality and quality of life (Donkor, 2018). This burden affects the daily life of survivors and their families and implies high health costs for governments (Rigby et al., 2009; Donkor, 2018).

Post-stroke cognitive and emotional complications are frequent consequences in the chronic stages of the disease. The prevalence of cognitive deficits one year after stroke ranges from 30 to 60%, depending on the study (Sexton et al., 2019). Furthermore, stroke significantly increases the risk of dementia in the long term (Pendlebury and Rothwell, 2009). Regarding emotional wellbeing, post-stroke depression and anxiety are common, being present in approximately one-third of the patients at any point in time (Ayerbe et al., 2013). Both cognitive and emotional disturbances are related to poor rehabilitation outcomes, morbidity, and mortality (Ayerbe et al., 2013; Obaid et al., 2020).

Consequently, it is fundamental to explore and test new health-behavior strategies to improve cognition and emotional wellbeing and prevent progressive cognitive decline and neurodegeneration after stroke. These strategies must be high-impact, low-cost, and easily accessible and implemented. Mindfulness, physical exercise (PE), and computerized cognitive training (CCT) have promising therapeutic potential in this scenario. These may benefit stroke patients by impacting neuroplasticity and brain health (Su and Xu, 2020).

Mindfulness is defined as “paying attention in a particular way: on purpose, in the present moment, and non-judgmentally” (Kabat-Zinn, 2003). Standardized interventions based on this concept [e.g., mindfulness-based stress reduction (MBSR)] have grown substantially in recent decades and have been successfully applied in healthy and clinical human populations, with benefits reported in a broad range of variables: mental health, cognition, pain, fatigue, physical health, and quality of life (Goldberg et al., 2022). In stroke, previous systematic reviews emphasize the potential utility of mindfulness in treating emotional disturbances (Lawrence et al., 2013), fatigue (Ulrichsen et al., 2016), and sensorimotor functions (Zou et al., 2018), while its benefits to cognition are still understudied.

The effects of mindfulness-based interventions may be explained by multiple biological pathways involving the cardiovascular, metabolic, inflammatory, and neuroendocrine systems (Reive, 2019). In healthy and clinical populations, the most frequently reported findings (not always in a consistent way) include reductions in circulating C-reactive protein (CRP), interleukin-6 (IL-6), and cortisol, and increases in brain-derived neurotrophic factor (BDNF) and insulin-like growth factor I (IGF-I) (Sanada et al., 2017; Reive, 2019). Meanwhile, neuroimaging studies have described structural and functional brain correlates of mindfulness in areas and networks related to attentional control, emotional regulation, and self-awareness (e.g., prefrontal and anterior cingulate cortex, amygdala, insula) (Tang et al., 2015). However, neither blood biomarkers nor brain data correlates of mindfulness have been addressed yet in stroke.

Physical exercise is considered a “planned, structured, and repetitive subtype of physical activity that aims to improve physical fitness” (Caspersen et al., 1985). Multiple systematic reviews and meta-analyses have shown the benefits of PE on cognition and emotional wellbeing across different age groups and health states (Rebar et al., 2015; Stillman et al., 2020). In stroke patients, contrarily to the effects of mindfulness, the gains of PE on cognition and emotional wellbeing have been more thoroughly studied. Some meta-analyses of randomized controlled trials have shown small-to-moderate effects of PE on cognition (Oberlin et al., 2017), depressive symptoms (Eng and Reime, 2014), and post-stroke health-related quality of life (Ali et al., 2021).

There might be a variety of processes behind the benefits of PE, including cellular and molecular, brain structure and function, and psychosocial mechanisms (Stillman et al., 2020). Biological mechanisms underlying cognitive and emotional benefits of PE include increased production of growth factors (e.g., BDNF, IGF-1), and decreased synthesis of pro-inflammatory molecules (e.g., CRP, IL-6), and accumulation of markers of neurodegeneration (Kandola et al., 2019; Stillman et al., 2020; Erickson et al., 2022). At a brain level, the positive influence of PE on the hippocampus and prefrontal gray matter volume (Erickson et al., 2014), global white matter volume (Sexton et al., 2016), and increased cross-network specificity across various functional networks (Stillman et al., 2019) have been described. Nevertheless, it should be noted that most of this evidence comes from studies with healthy older adults. In stroke, knowledge is still scarce, with preliminary findings in animal models and clinical studies focusing mainly on motor recovery (Xing and Bai, 2020).

Computerized cognitive training consists of repeated practice of standardized cognitive exercises that can be performed through the computer or mobile technology (Gates and Valenzuela, 2010). CCT has rapidly evolved in the last decade because of its potential to systematically apply personalized cognitive rehabilitation and its straightforward implementation in at-home use (Solana et al., 2015). In stroke care, multiple systematic reviews and meta-analyses have addressed the potential benefits of CCT in cognitive functioning (Mingming et al., 2022). However, although promising, results remain inconclusive due to study heterogeneity and methodological limitations. Some authors have further analyzed the additive gains of combining CCT with PE in stroke patients, with preliminary positive results (Amorós-Aguilar et al., 2021).

From a molecular and brain perspective, applying CCT following a stroke is based on the idea that repetitive cognitive tasks might promote neuroplasticity mechanisms and restore impaired cognitive function (Sigmundsdottir et al., 2016). Based on animal models using enriched environments, some authors hypothesize that cognitive stimulation promotes the release of growth factors (e.g., BDNF and nerve growth factor) which, in turn, enhances cell survival and proliferation in human brains (Valenzuela et al., 2007). Few studies have shown structural and functional brain changes after applying CCT to stroke (van de Ven et al., 2016), while others have fallen to prove any changes in neuroimaging data (Nyberg et al., 2018).

To conclude, cumulative evidence indicates that mindfulness, PE, and CCT could be effective strategies against post-stroke cognitive impairment and emotional disturbances. Nonetheless, it is necessary to conduct new randomized controlled trials to confirm and deepen these benefits and elucidate the biological mechanisms (i.e., metabolic, immune, cardiovascular, neuroendocrine) by which they occur. As a step forward, the inclusion of gut microbiome data, which seems to be affected in stroke patients (Lee et al., 2021) and might be modified by lifestyle behaviors (Manor et al., 2020), will offer new and valuable insights into stroke pathophysiology and rehabilitation.

## Aims of the study

The primary objective of the MindFit Project is to examine the effects of MBSR and PE on cognitive and emotional outcomes in chronic stroke patients by comparing three groups of participants who receive: MBSR + CCT, PE + CCT, or CCT alone. The primary hypotheses sustaining our main objective are:

(1)All three groups will experience gains at 3 months compared to baseline in cognitive functions and emotional status.(2)Given the study design (i.e., all three groups receive the same CCT treatment, with the only difference being the addition of either MBSR or PE), these improvements in cognition and emotion will be greater in the combined treatment groups than in the only CCT group (either to a greater extent in the same outcomes or different cognitive and emotional measures).(3)The add-on effects of MBSR and PE will differ from each other (i.e., they will have a specific profile of cognitive and emotional gains). Although there is a lack of studies comparing mindfulness and PE, we expect greater emotional gains after MBSR than PE, while PE will produce more cognitive benefits than MBSR.

The secondary objectives of the MindFit Project are:

(a)To study intervention-related changes in the molecular-cellular level (e.g., cardiometabolic, inflammatory, neurotrophic factors, gut microbiome species), the brain level [i.e., structural and functional magnetic resonance imaging (MRI)], and the behavioral level (e.g., physical activity and fitness status, mindful thinking, sleep quality, fatigue, quality of life).(b)To examine whether changes in the molecular-cellular, brain and behavioral levels mediate cognitive and emotional intervention-related changes.(c)To determine the genetic [i.e., apolipoprotein E (APOE) genotype], clinical (e.g., comorbidities, level of brain atrophy), sociodemographic (e.g., sex, age, educational level), and individual factors (e.g., cognitive reserve, general intelligence, personality), that moderate cognitive and emotional intervention-related changes.

A graphical representation of our objectives is presented in Figure 1.

**FIGURE 1 F1:**
[figure not shown]
MindFit project graphical objectives. APOE, apolipoprotein E; BDNF, brain-derived neurotrophic factor; CCT, computerized cognitive training; CRP, C-reactive protein; IGF-I, insulin-like growth factor I; IL-6, interleukin-6; MBSR, mindfulness-based stress reduction; PE, physical exercise; VEGF, vascular endothelial growth factor.

## Materials and methods

### Study oversight and schedule

The MindFit Project is a prospective, parallel, three-arm, single-blinded randomized controlled trial. The trial consists of three groups in total, of which two are intervention groups, and one is the active control group. One hundred forty-one participants at three to 60 months after stroke are randomly allocated to one of three arms (1:1:1 allocation ratio). The first intervention group receives an MBSR program combined with CCT; the second intervention group receives a multicomponent PE program combined with CCT; and the third group, as an active control group, receives only CCT. The interventions last 12 weeks, with assessments at baseline and within two weeks after completion of the trial (see Figure 2). This study is led by the Faculty of Psychology of the University of Barcelona in collaboration with Hospital Universitari Germans Trias i Pujol and Institute Guttmann. The responsible ethics committees approved it following the Declaration of Helsinki. This protocol follows the SPIRIT recommendations (Chan et al., 2013).

**FIGURE 2 F2:**
[figure not shown]
MindFit project study design. CCT, computer-based cognitive training; MBSR, mindfulness-based stress reduction; PE, physical exercise.

### Deviation from the initial protocol

The MindFit Project was initially planned to be entirely onsite. However, all interventions and most assessments (i.e., all of them except for biological sample collection and brain scans) had to be converted to online versions because of the COVID-19 pandemic. The biological sample collection laboratory and the MRI center remained open with extra protective measures during the pandemic.

We followed international recommendations to adapt assessments and interventions to the virtual context. Furthermore, we ran several pilot groups to practice and improve our protocols according to participants’ feedback. Finally, the project started in November 2020, and data collection was completed in December 2021 (see NCT04759950 in www.ClinicalTrials.gov for the entire study version history; first posted on February 18, 2021).

### Participants

Inclusion and exclusion criteria are detailed in Table 1. Based on stroke epidemiology (Feigin et al., 2017), we anticipated approximately 60% of the sample to be men and 80% of cases to be ischemic strokes.

**TABLE 1 T1:** Eligibility criteria.

Inclusion criteria	Exclusion criteria
• Women and men aged 18–80 years old • Diagnosis of ischemic or hemorrhagic stroke • Stroke diagnosis between 3 and 60 months ago • To have consent from a physician to engage in an exercise intervention • Fluency in Catalan or Spanish (i.e., able to understand and speak) • Accept to participate in the study and sign the informed consent according to the Declaration of Helsinki	• Cognitive impairment defined as a score in Mini-Mental State Examination ≤23 (Blesa et al., 2001) • Severe aphasia defined as a score ≥2 in item 9 of the National Institute Health Stroke Scale (Montaner and Alvarez-Sabín, 2006) • Severe sensory problems • Diagnoses of transient ischemic attack without evidence of brain lesion • Other neurological conditions apart from stroke (e.g., traumatic brain injury, brain tumors) • Severe pre-stroke psychiatric disorders (e.g., bipolar disorder, schizophrenia) • History of alcohol or other substance abuse

After the recruitment phase, we achieved our desired sample size. One hundred forty-one stroke patients from Catalonia and other regions in Spain had a baseline assessment and were randomized to one of the three study arms. We will report the final numbers and the flow diagram of study recruitment in our first paper with the primary outcome results.

### Recruitment and screening

We recruited stroke patients through advertising on social media, publicity, and contacting hospitals and stroke and acquired brain damage patient associations. Before the COVID-19 pandemic, we adopted a local strategy based on publication in the local press and obtaining participants from patient lists of general physicians in the Metropolitan Area of Barcelona. After the pandemic’s start, the recruitment process focused mainly on social networks, expanding the target population to the entire Catalan territory. This change in strategy accelerated the recruitment process and allowed for a larger sample with a more extensive geographic representation.

Interested people contacted the study investigators by telephone, email, or social networks. Patients interested in participating received oral and written detailed information about the study and were asked to fulfill a screening questionnaire to determine if they met the admission criteria. Subsequently, we invited potential participants to a teleconference visit where an evaluator administered the Mini-Mental State Examination (Blesa et al., 2001) and exhaustively reviewed the rest of the study criteria. If candidates were eligible, the information about the study was provided again, and any questions were answered. The informed consent form was signed if the participant agreed to engage in the project. Afterward, an alphanumeric code in the order of arrival was assigned to the participant.

### Assessments

Within two weeks before the interventions started and within two weeks after completing the interventions, we performed medical, cognitive, and physical assessments, neuroimaging, and biological samples collection. When possible, we evaluated patients who dropped out of the study in the follow-up assessment to comply with the intention-to-treat principle.

All the assessments were online except for brain scans, blood tests, and stool sample collection, which were done with extra safety measures at the Hospital Universitari Germans Trias i Pujol (Barcelona, Spain). We conducted online assessments through the Zoom platform (except for medical and physical visits, which were done using a hospital-specific platform). A few days before the assessment, we communicated to the participants the electronic platform which would be used, the link to access the virtual room, and any material they needed to have ready for the visit (e.g., printed documents or objects to do the physical tests).

The assessment timeline is presented in Table 2. Assessors received specific training and a written protocol of the assessment schedule and instructions. The same evaluators carried out the baseline and post-intervention measurements to minimize bias from inter-rater variability.

**TABLE 2 T2:** Assessments schedule.

	Enrollment and screening		Baseline assessments (within 2 weeks prior to the start of the intervention)					Intervention (12 weeks)	Post-intervention assessments (within 2 weeks after the end of the intervention)				
				
	Screening (telematic)	Visit 0 (telematic)	Visit 1 (telematic)	Visit 2 (telematic)	Visit 3 (telematic)	Visit 4 (in-person)	Visit 5 (in-person)		Visit 6 (telematic)	Visit 7 (telematic)	Visit 8 (in-person)	Visit 9 (in-person)	Visit 10 (telematic)
Information of study	✓	✓											
First review of criteria	✓												
Exhaustive review of criteria		✓											
Informed consent form		✓											
Medical story			✓										
General health status			✓							✓			
Neuropsychological tests				✓					✓				
Cognitive scales				✓					✓				
Psychological scales				✓					✓				
Anthropometric measures					✓					✓			
Physical fitness tests					✓					✓			
Lifestyle behaviors scales					✓					✓			
Blood extraction						✓					✓		
Stool sample collection						✓					✓		
Magnetic resonance imaging							✓					✓	
Intervention follow-up diary								✓					
Exercise bracelet								✓					
Qualitative interviews													✓

### Randomization and blinding

After baseline assessments, an independent biostatistician randomized the participants into the three groups through a simple randomizing procedure with an equal allocation ratio (i.e., 1:1:1; 47 individuals per arm) created with a random sequence generator software. We did not use any stratification method due to practical reasons. The randomization sequence was stored on an institutional server and was password protected. Only the person in charge of the randomization, who was not involved in either evaluation or intervention tasks, had access to it.

Group allocation remained blind for all outcome assessors and data analysts, while participants and care providers could not be masked due to the nature of the interventions. Participants received instructions not to discuss any activities related to the intervention with the outcome assessors during the follow-up assessments.

### Interventions

The interventions consisted of five daily sessions per week for 12 weeks and were performed entirely remotely. The mindfulness group received an MBSR program combined with CCT; the PE group received a multicomponent PE program combined with CCT, and the control group only received CCT. The duration of the combined interventions was approximately twice that of the active control group. In the two combined therapy groups, participants did not receive any specific instructions regarding the order in which to perform the interventions.

Mindfulness-based stress reduction and PE interventions included (a) online synchronous sessions guided by expert caregivers and done in groups of 8–12 participants and (b) individual autonomous sessions. In contrast, the control group performed all sessions independently through a computerized telerehabilitation platform. To minimize the confounder effect of benefits from peer interaction and social support in the combined interventions, we invited participants from the same intervention arm to communicate and share experiences through WhatsApp groups.

Before starting the interventions, participants were instructed to use the electronic platforms. Furthermore, they were provided with a manual that collected the main instructions, safety measures to perform the assigned therapies, and a compendium of doubts and frequently asked questions resolved.

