### Analysis

#### Power analysis

Sample size calculations were conducted using the Granmo v7.12 software. Accepting an alpha risk of 0.05 and a beta risk of less than 0.20 in a bilateral contrast, 47 participants in each group are required to detect a minimum difference of 0.75 standard deviations between each pair of groups (assuming that there are three) after standardization of the variables to have mean 0 and standard deviation 1. This sample size supports a 20% tracking loss rate. We established a minimum effect size of 0.75 standard deviations by considering the results of meta-analyses studying the effects of mindfulness or PE on cognition or emotional wellbeing in stroke patients (e.g., Abbott et al., 2014; Oberlin et al., 2017; Ali et al., 2021; Sun et al., 2021). The effect sizes reported in these papers range from small-moderate (between *d* = 0.30 and *d* = 0.50) to moderate-large (between *d* = 0.50 and *d* = 1), depending on the intervention and the outcome studied. We used an intermediate effect size that was realistic to the literature and satisfied our trial’s practical and economic possibilities.

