#### Statistical analysis

Statistical analysis will be carried out with IBM statistical package for the social sciences (SPSS) Statistics 27 and R environment. The same statistical pipeline will be run twice, in two sequential phases: (1) intention-to-treat analysis considering data from all randomized participants, including those that complete and drop out of the study (in case of missing values, an adequate method of imputation will be executed whenever appropriate, depending on the proportion of missing data and the missingness mechanisms); (2) per-protocol analysis including only those who have had a treatment adherence equal to or higher than 80%. The significant threshold will be set at a two-tailed *p*-value of 0.05, and an appropriate multiple comparisons correction method will be implemented.

Baseline demographic and clinical characteristics of participants in the different intervention groups will be described with central tendency, dispersion, and position measures and compared between the three groups using parametric or non-parametric tests. To address our primary hypotheses, we will use multiple regression models, which will include: (a) the difference between the follow-up and baseline values in the primary outcome measures as the explained variable; (b) the 3-arms intervention as the explaining variable, and (c) other confounding factors as covariates. We will consider sex, age, years of education, time since stroke, and the baseline score as fixed covariates. Moreover, we will contemplate the need to adjust for further unbalanced factors between groups that appear to correlate strongly with the outcomes. In case of violating the linear regression assumptions, transformations of the variables or methods of robust regression will be adopted. We will examine the secondary outcomes with the same pipeline in the per-protocol sample. Although the sample size was not calculated to allow interaction effects, we will examine potential mediator and moderator effects in this sample.

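### MBSR and PE are delivered partly in therapy groups, but the primary regression and the sample size assume independent participants; if outcomes correlate within groups, between-arm standard errors are too small

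*Protocol article*

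**What the plan says.** All references are to the protocol article.

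- **Allocation.** Individuals are randomised 1:1:1, 47 per arm (Randomization and blinding).
- **Delivery.** The MBSR and PE programmes included "online synchronous sessions guided by expert caregivers and done in groups of 8–12 participants", plus individual sessions. By contrast, "the control group performed all sessions independently through a computerized telerehabilitation platform" (Interventions).
- **Analysis.** "To address our primary hypotheses, we will use multiple regression models" (Statistical analysis). The dependent variable is the change score and the predictor is the three-level arm factor. The fixed covariates are sex, age, education, time since stroke and baseline score. Further covariates enter only if they are unbalanced between arms and related to outcome. If linear-regression assumptions fail, the fallback is transformation or robust regression. Therapy group appears nowhere.
- **Sample size.** The calculation is two-sided at alpha 0.05 with power of at least 80%, and outcomes are scaled to SD 1. It concludes that "47 participants in each group are required to detect a minimum difference of 0.75 standard deviations between each pair of groups" (Power analysis). The same section allows for 20% loss to follow-up. No design effect or within-group correlation is mentioned.

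**The concern.** This is a partially nested design: individuals are randomised, but in two of the three arms they are then treated together. Members of a live group share sessions and peers, so their outcomes may be more alike than those of two people drawn from the arm at large. The protocol itself treats peer interaction and social support as possible sources of benefit in the combined arms.

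An ordinary regression counts every participant as a separate piece of information. With positive within-group correlation it understates the variance of an arm mean in the MBSR and PE arms. Confidence intervals for between-arm contrasts are then too narrow and p-values too small. MBSR vs PE, which carries the third primary hypothesis, has both arms grouped and is affected most. The CCT arm's own change from baseline is not affected.

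**Working it through.** **Inputs from the protocol article.** 47 per arm, difference 0.75 SD, SD 1, two-sided alpha 0.05, power at least 80%, loss 20% (Power analysis). Group size 8–12 (Interventions). Since 47/12 = 3.9 and 47/8 = 5.9, an arm of 47 makes four or five groups; six groups of 8 would need 48 people. Five groups average 47/5 = 9.4 members.

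**Assumed.** ICC from 0 to 0.10; the document gives none.

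**Step 1: reproduce 47.** n = 2(z_α + z_β)²/0.75².
- Unadjusted alpha 0.05: 2(1.960 + 0.842)²/0.5625 = 27.9, so 28; 28/0.8 = 35. This does not match.
- Alpha 0.05/3 for three pairs: 2(2.394 + 0.842)²/0.5625 = 37.2; 37.2/0.8 = 46.5, so 47. This matches.

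The stated figure therefore fits a Bonferroni-type alpha (inferred, not stated) and a design effect of 1, i.e. independent participants.

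**Step 2: variance inflation.** In a grouped arm, DE = 1 + (m − 1) × ICC. The ratio of true to naive standard error is √((1 + DE)/2) for a combined arm vs CCT and √DE for MBSR vs PE. Actual type I error is 2Φ(−1.96/ratio).

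Example, ICC 0.05 and m = 9.4: DE = 1 + 8.4 × 0.05 = 1.42. The ratios are √1.21 = 1.10 and √1.42 = 1.19. The errors are 2Φ(−1.78) = 7.5% and 2Φ(−1.64) = 10.0%.

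| ICC | SE ratio: vs CCT / MBSR vs PE | Type I error, formula | Type I error, simulated |
|---|---|---|---|
| 0 | 1.00 / 1.00 | 5.0% / 5.0% | 5% / 5% |
| 0.01 | 1.02 / 1.04 | 5.5% / 6.0% | 5.5% / 6.2% |
| 0.05 | 1.10 / 1.19 | 7.5% / 10.0% | 7.5% / 9.8% |
| 0.10 | 1.19 / 1.36 | 10.0% / 14.9% | 10% / 14.7% |

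The simulation used 40,000 three-arm trials per setting, with five groups in each combined arm, zero mean arm effects and least squares without covariates. The overall three-arm F test gave 6.0%, 9.5% and 14.4% at ICC 0.01, 0.05 and 0.10. With four groups per arm, ICC 0.05 gave about 8.4%/11.6%. After 20% loss (38 per arm, five groups) it gave about 7%/9%.

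**Step 3: power after 20% loss.** n = 37.6 per arm, m = 7.52, alpha 0.05/3, power = Φ(0.75/SE − 2.394).
- ICC 0: SE = √(2/37.6) = 0.231; power 80%.
- ICC 0.05: DE = 1 + 6.52 × 0.05 = 1.326.
  - vs CCT: SE = √(2.326/37.6) = 0.249; power 73%.
  - MBSR vs PE: SE = √(2 × 1.326/37.6) = 0.266; power 67%.
- ICC 0.10: power 67% and 55%.

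These power figures make no allowance for the few degrees of freedom that 4–5 groups per arm provide, so they are optimistic.

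**The case against.** A reader might infer that the standard errors are too small as a matter of fact, and that type I error exceeds 5% in every primary comparison. The document does not support that.

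- **No ICC is given.** At ICC 0 the error is exactly 5%, and at 0.01–0.02 it is about 5.5–7%. This stands: the point is conditional.
- **Much of the treatment is individual.** All CCT is done alone, as are four of five MBSR days in a typical week and two of five PE sessions. This stands as a reason to expect a modest ICC. By time, though, a typical MBSR week has 150 group minutes against 4 × 20–40 = 80–160 individual minutes, so 48–65% is in the group.
- **Individual randomisation protects the test.** If no treatment or group affects anyone, the test stays close to valid. But the null for MBSR vs PE is equal mean effects of two treatments both expected to work, and group-specific effects can vary around that null. Interval coverage for non-zero effects is not protected either.
- **Some sources of correlation may not vary by group.** If the same staff led every group in an arm, instructor is confounded with arm, and a therapy-group term cannot repair that. The WhatsApp groups were organised by arm. Calendar effects may be shared with CCT. These points weaken the case for a large ICC, but shared sessions and group peers remain.
- **Robust regression might cover dependence.** Independence is a regression assumption and the robust method is not named. As usually understood, however, the term deals with outliers or error shape, and no cluster adjustment is mentioned.
- **An article condenses.** It does, but this one fixes the model, outcome, predictor, covariates and fallback, so this is a stated choice rather than an omitted detail.

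**Conclusion.** The point holds in conditional form. Delivery is partially nested, while the stated model and sample size assume independence. If outcomes correlate within therapy groups, between-arm inference is too optimistic, and MBSR vs PE suffers most. The inflation is slight at ICC 0.01 and becomes material from about 0.05, where type I error is roughly 7–7.5% against CCT and 9–10% for MBSR vs PE, depending on loss. These figures rest on the assumed ICC values, five near-equal groups per combined arm, and group effects that vary around a zero mean difference. The document neither establishes nor excludes such a correlation. It does not show that the trial's conclusions will be wrong, only that the planned analysis neither models nor checks for it.

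**What to change.** - Add each participant's therapy group to the analysis data. Instructors recorded class attendance (Intervention adherence), so membership should be recoverable, although the article does not say that it is held as a variable.
- Fit the between-arm primary comparisons as a partially nested mixed model: a random intercept for therapy group in MBSR and PE, CCT participants as singletons, and small-sample degrees of freedom (Satterthwaite or Kenward–Roger). Keep the same fixed covariates and report the ICC.
- State in Power analysis that 47 per arm assumes no within-group correlation. Data collection ended in December 2021, so the sample size cannot be raised.

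**Cost.** The change needs analysis wording and a group identifier, and no new data collection. Intervals will be wider. With 4–5 groups per arm the group variance will be poorly estimated and may come out at zero, which returns the ordinary regression. Group identifiers also reveal the CCT arm, whereas the article keeps data analysts blind to allocation. Lock the model code before the identifiers are released, or have an unblinded statistician run it.
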